#### Measuring morbidity and lifestyle

Alcohol abuse or dependency: the AUDIT is a 10-item questionnaire designed to screen for excessive drinking. It takes 2 minutes to complete, with scores of 15 or greater indicating harmful alcohol use or dependency [36]Medical morbidities, medications and lifestyle: we will collect information about demographics, lifestyle (smoking, alcohol use, body mass index), common medical conditions diagnosed by a doctor, and medications used (including use of illicit substances). This questionnaire takes approximately 5–10 minutes to completeDetails of surgery: we will record the type of surgery and total length of surgical procedure including duration on bypass (if applicable)Medications: we will record participants’ medications on admission and discharge. We will also record the use of all psychiatric medications during hospitalizationReferral to mental health or geriatric services during admission will be recordedLength of stay (LOS): we will record total hospital stay duration and intensive care unit (ICU) length of stay in hours for participants discharged alive from hospitalDestination post discharge: we will record destination post discharge for all participants and, for the purposes of analysis, will group them into “discharge to usual place of residence” versus “discharge to other places.” Participants who die following cardiac surgery will form a separate groupCognition: this will be measured with the TICS-m. The TICS-m is a brief, widely used telephone assessment instrument with good reliability and validity to screen for dementia and cognitive impairment in older people [40]. It can be rated in person or by telephone. It consists of 13 items measuring various aspects of cognitive function yielding a total score of 50. Scores ≤27 indicate the presence of clinically significant cognitive impairment. Cognitive function will be measured at baseline, discharge and 3 months after surgery. The TICS-m was chosen to allow us to assess participants’ cognition 3 months after surgery in the comfort of their own homes. We deliberately chose this approach to reduce participant burden and improve study retention. In addition, many Western Australian patients live in country areas so that in-person attendance would be difficultDepressive and anxiety symptoms: we will measure depressive and anxiety symptoms at baseline, discharge and at 3 months with the Hospital Anxiety and Depression Scale (HADS) [41]. This is a self-report scale of 14 items in total that gives sub-scores for both depression and anxiety

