### Sample size

The primary outcome of the proposed trial is the development of delirium within 7 days of surgery. We based our sample size on the trial of Al-Aama and colleagues [31]. They reported a 15.6 % absolute reduction (19.2 % versus 3.6 %, *p* < 0.02) in the incidence of delirium in their sample. Assuming a 15.6 % absolute risk reduction in our patients with a conservative 25 % incidence of delirium in the control group and an incidence of 9.4 % in the intervention group, we will require 91 participants per group (182 participants in total) to detect a difference of this magnitude with a power of 80 % and a two-sided alpha of 0.05. After allowing for a conservative loss to follow-up of 15 % [31], we calculated that we will need to recruit 210 participants (105 per group). A defined secondary outcome for this trial is cognitive performance 1 week and 3 months after surgery. A study with 100 participants per group at the 3-month follow-up will have 81 % power to declare as significant between group difference of 2 points in the change from baseline score of the TICS-m (1 versus 3 points, SD 5). A change of less than 2 points would be of uncertain clinical significance.

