### Allocation, randomization, blinding and compliance

Participants will be randomized to treatment with melatonin or placebo in a ratio of 1:1 according to a list of computer-generated random numbers in permuted blocks ranging from 8 to 12. This strategy decreases the risk of unblinding of participants in one particular block if, for some reason, the group membership of one of its members is disclosed. The list will be generated and maintained by an independent biostatistician.

The pharmacy will dispense melatonin or placebo. Melatonin and placebo will be administered as oral capsules that have the same size, weight, color, texture and taste. The active medication will consist of 3 mg melatonin. These will be manufactured in batches every 12 months with 6-monthly stability testing performed for weight, disintegration, impurities and appearance. The pharmacy will be responsible for dispensing all study medications, which will be included on the patient medication chart as per usual hospital practice. Unblinding will only occur once the final endpoint of interest is collected from the last participant in the trial. Compliance will be encouraged through a telephone call to each participant 2 days prior to his or her scheduled surgery date. Participants will be reminded to take their tablets and will be asked to bring the remainder into hospital for use following their surgery. Participants will be given ten tablets to allow for the possibility of surgery being postponed once they have commenced taking the trial medication. We will record all incidences where participants take extra tablets beyond the scheduled seven. Treatment adherence will be determined by the systematic review of medication charts upon discharge and by pill count. Use of sedative/psychotropic medications outside of the study protocol will also be recorded.

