### Statistical methods

We will analyze and store the data using reliable statistical software (Stata, StataCorp, College Station, TX, USA). Baseline data will be compared using descriptive statistics, Student *t* tests for normally distributed continuous variables, the Mann-Whitney test for ordinal variables and Pearson’s chi-square statistic for categorical variables. The primary outcome analysis will be intention-to-treat and will use multilevel logistic regression of panel data (xtlogit). This approach to the analysis of the data allows for the inclusion of all available information and for the investigation of interactions between terms (such as intervention and time). A similar approach will be used to analyze other binary outcomes (e.g., use of psychotropic medication). We will use multilevel mixed models to investigate changes in scores of the MDAS and TICS-m (continuous variables). All probability tests will be two-tailed and will be declared as significant when *p* < 0.05.

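### The 3-month TICS-m comparison is powered on an unadjusted change from baseline and no baseline adjustment is stated for its mixed model; stating one would be a free gain in precision

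*Protocol article*

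**What the plan says.** All places are in the protocol article.

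- **Measurement.** Under Measuring morbidity and lifestyle: "Cognitive function will be measured at baseline, discharge and 3 months after surgery". TICS-m is also used for eligibility (scores of 19 or below are excluded), so a pre-treatment score should exist for every participant.
- **Power.** Sample size gives TICS-m a power statement of its own, the only secondary outcome to have one. "A study with 100 participants per group at the 3-month follow-up" "will have 81 % power to declare as significant" a "between group difference of 2 points in the change from baseline score of the TICS-m (1 versus 3 points, SD 5").
- **Analysis.** Statistical methods: "We will use multilevel mixed models to investigate changes in scores of the MDAS and TICS-m (continuous variables"). The section does not define the response, lists no fixed effects, and neither includes nor excludes the baseline score. Earlier in the same section, interactions such as intervention by time are mentioned, but for the binary primary model.
- **Test.** "All probability tests will be two-tailed and will be declared as significant when *p* < 0.05".

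**The concern.** Both the sizing and the analysis text are worded in terms of change. Two natural ways to carry that out are to take the change score as the response, or to take all three visits as responses with an unrestricted group-by-time term. With complete data both give the difference in mean change, which fixes the slope on baseline at 1. Using the measured baseline as a covariate lets the data set that slope. It estimates the same between-arm difference, usually with a smaller standard error. At stake is precision on the trial's cognitive outcome, at the 2-point difference below which the plan itself doubts clinical significance. The primary delirium analysis is not affected.

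**Working it through.** **Inputs.** From the plan: difference 2 points (3 − 1), SD of change 5, 100 per group, 1:1 allocation, two-sided alpha 0.05. Assumed, because the documents do not give them: rho, the correlation of baseline with 3-month TICS-m, and k, the ratio of baseline SD to follow-up SD.

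**1. The plan's own figure.** Standard error = 5 × √(2/100) = 0.707, and 2/0.707 = 2.83. Power is 80.7% by the normal approximation and 80.4% by the noncentral t. The stated 81% reproduces.

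**2. Direction.** Let β be the true slope of follow-up on baseline, σ_B the baseline SD and σ_R the residual SD about that slope.

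- Variance per person, baseline-adjusted: σ_R²
- Variance per person, change score: σ_R² + (1 − β)²σ_B²

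The extra term is never negative and is zero only at β = 1. This is a large-sample statement; estimating the slope costs one degree of freedom per visit.

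**3. Size with equal variances (k = 1).** Then β = rho. The change-score variance is 2σ²(1 − rho) and the adjusted variance is σ²(1 − rho²), so their ratio is (1 + rho)/2. The adjusted SD is 5 × √((1 + rho)/2).

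| rho | adjusted SD | power at 100 per group (t to normal) |
|---|---|---|
| no adjustment | 5.00 | 80.4% to 80.7% |
| 0.5 | 4.33 | 90.1% to 90.4% |
| 0.7 | 4.61 | 86.3% to 86.6% |
| 0.9 | 4.87 | 82.3% to 82.7% |

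**4. Size with a smaller baseline SD.** Here β = rho/k and the variance ratio is (1 − rho²)/(1 + k² − 2·rho·k). Power by the noncentral t at 100 per group, with the SD of change held at 5:

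| rho | k = 0.9 | k = 0.8 |
|---|---|---|
| 0.5 | 87.3% | 84.6% |
| 0.7 | 83.2% | 81.1% |
| 0.8 | 81.4% | 80.4% |

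At k = 0.8 and rho = 0.8 the ratio is 0.36/0.36 = 1. The slope is 1 and nothing is gained.

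**5. Does the mixed model settle it?** Take three visits, complete data, equal correlation rho = 0.6, raw SD 5 (chosen for illustration) and 100 per group.

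- Baseline as a response with a free arm difference at baseline: SE 0.632. The change score gives 5 × √(2 × 0.4) × √(2/100) = 0.632.
- Baseline as a response with a common mean across arms: SE 0.566. Baseline as covariate gives 5 × √(1 − 0.36) × √(2/100) = 0.566.

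The words "multilevel mixed model" therefore cover both the less and the more efficient analysis.

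**6. Chance imbalance.** If the arms differ by D at baseline, the change-score estimate is expected to miss by (β − 1)D. Over randomizations D averages zero with variance 2σ_B²/n, so this term has mean zero and variance (1 − β)²σ_B² × 2/n. That is exactly the extra variance in step 2.

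**The case against.** - **The analysis section is silent; it does not refuse adjustment.** This stands. A reader might infer that the plan discards the baseline score, but the text does not say so. The sentence also covers MDAS, where change most naturally means a course over repeated ratings. A repeated-measures model with a common baseline mean would fit the wording too.
- **An article leaves covariate lists to the full protocol or analysis plan.** This stands for a bare missing list, and is why the point is a proposal and not an error. What remains is that the article commits to change from baseline in the power statement and repeats the language of change in the analysis. The natural readings of that lead to the less efficient form.
- **The power statement is correct.** This stands. Sizing on an unadjusted change is conservative and does not bind the analysis.
- **The gain may be negligible.** This stands as a limit on size. The (1 + rho)/2 rule needs equal variances, and excluding low TICS-m scores at entry could make the baseline SD the smaller one. Step 4 shows the gain can then be nil. The direction is unaffected.
- **Randomization already deals with imbalance.** This stands as regards bias. A reader might infer that unstratified allocation biases the change-score result. It does not on average: the conditional error in step 6 is the same loss of precision and must not be counted twice.

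**Conclusion.** The point holds as a free improvement to a secondary analysis. Without a stated baseline adjustment, the readings closest to the text give up precision whenever the true slope on baseline differs from 1, and in large samples they never gain any. At 100 per group with equal variances, adjustment raises power from about 80–81% to about 90% (rho 0.5), 86–87% (rho 0.7) or 82–83% (rho 0.9). With a baseline SD below the follow-up SD the increase is smaller and can be zero. Every one of these gains rests on assumed correlations and SDs.

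The documents do not support saying that baseline is excluded from the model, that the 81% is wrong, or that the treatment effect would be biased. The 81% can stay as a conservative figure for 100 per group. Whether 100 per group will be reached is a separate question, since 105 less the plan's 15% loss is about 89.

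**What to change.** In Statistical methods, state that TICS-m at discharge/day 7 and at 3 months is analysed with a mixed model having treatment, visit, treatment-by-visit, baseline TICS-m and baseline-by-visit as fixed effects. Alternatively, keep all visits as responses and constrain the arms to a common baseline mean. Report the adjusted between-arm difference at 3 months. In Sample size, keep the 81% and label it as the power of the unadjusted change score at 100 per group.

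The cost is one sentence in the analysis text and, for the covariate form, two degrees of freedom. No extra participants, visits or data are needed, and the quantity estimated (the between-arm difference in mean change) stays the same.

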### Data monitoring and safety

We will monitor adverse effects with a checklist of symptoms commonly associated with experimental medications, such as tremor, headaches, anxiety, insomnia and gastrointestinal symptoms. The participants will be asked about the emergence of any new symptoms since the last assessment and how much they have been bothered by them: not at all, a little, quite a bit and extremely. The checklist will be completed prior to enrollment and at discharge. The investigators will use this to screen for any new symptoms that could be attributed to the study medication. Melatonin is a naturally occurring hormone and the incidence of serious adverse events is expected to be low. An independent, unblinded data monitoring committee, chaired by an independent academic biostatistician, will be established to oversee the safety of participants in the trial. This committee will meet twice per year. Using statistical criteria for acceptable deviations from the null hypothesis, the committee will advise the investigators whether the recruitment can continue or whether the study should be terminated.

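### As worded, the adverse-effect checklist asks about, grades and screens only new symptoms, so worsening of a symptom already present at baseline may go unrecorded

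*Protocol article*

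**What the plan says.** The section on data monitoring and safety in the protocol article describes the whole procedure in a few sentences.

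- **Instrument:** a "checklist of symptoms commonly associated with experimental medications, such as tremor, headaches, anxiety, insomnia and gastrointestinal symptoms".
- **Question:** "The participants will be asked about the emergence of any new symptoms since the last assessment and how much they have been bothered by them".
- **Grades:** "not at all, a little, quite a bit and extremely".
- **Timing:** "The checklist will be completed prior to enrollment and at discharge". Table 1 agrees: adverse events are marked only at baseline and at discharge or 7 days after surgery.
- **Use:** "The investigators will use this to screen for any new symptoms that could be attributed to the study medication".

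Neither this section nor the one on statistical methods says how a participant is classed as having an adverse effect, and neither describes a comparison of adverse effects between arms.

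**The concern.** The restriction to new symptoms appears twice, once in what is asked and once in what is screened. In the question, the bother grade attaches to the new symptoms. Worsening of a symptom that was already there is not mentioned in the article.

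The named symptoms are ones that people can plausibly have before the first capsule. Participants are aged 50 and older and awaiting coronary or valve surgery, and some are already inpatients after a myocardial infarction or with unstable angina. Anxiety, insomnia and headaches at baseline would be no surprise, although the article gives no prevalence. Insomnia deserves particular attention because the background section describes melatonin as a regulator of the sleep-wake cycle.

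What is at stake is tolerability. The discussion anticipates that melatonin may prove safe for patients at high risk of delirium. A screen that registers a trivial new symptom but has no stated place for a marked worsening of an old one gives weaker support for that conclusion than the same form could give. Unlike an analysis detail, this cannot be left until later: a grade that was not collected at discharge cannot be reconstructed.

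**Working it through.** No stated figure depends on this point, so there is none to reproduce. The check is a reading of the text, followed by an illustration of size.

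**Step 1: what the wording covers.** Three participants, with the sentences applied as they stand:

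| Before enrollment | At discharge | New? | Within the question and the screen as worded? |
|---|---|---|---|
| No insomnia | Insomnia, a little | Yes | Yes |
| Headache, a little | Headache, quite a bit | No | No |
| Insomnia, a little | Insomnia, extremely | No | No |

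The smallest new symptom is covered and a two-grade worsening is not.

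**Step 2: whether the design points the same way.** Two completions with a graded scale are suited to measuring change from baseline. A question about symptoms new since the last assessment also has no reference point at the pre-enrollment completion, because no assessment precedes it. So either the items are graded at both times regardless of novelty, and the sentence describes the form wrongly, or the form follows the sentence, and the baseline grades have little to be compared with. The article does not settle which. The sentence needs repair in both cases.

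**Step 3: other coverage.** The HADS is given at baseline, discharge and 3 months, so a rise in anxiety would be measured there, as an outcome rather than as part of the adverse-effect screen. Sleep is one of nine areas rated by the daily CAM, for the diagnosis of delirium. The article describes no repeated measure of headache, tremor or gastrointestinal symptoms other than the checklist.

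**Step 4: illustrative size.** The group size of 105 comes from the sample-size section. Baseline prevalence *b* and the proportion *w* of those participants who worsen are assumptions.

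- Participants per group who cannot report the symptom as new = 105 × *b*
- Worsened participants missed per group = 105 × *b* × *w*

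| *b* | 105 × *b* | Missed at *w* = 10 % | Missed at *w* = 30 % |
|---|---|---|---|
| 10 % | 10.5 | 1.1 | 3.2 |
| 30 % | 31.5 | 3.2 | 9.5 |
| 50 % | 52.5 | 5.3 | 15.8 |

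These figures are for one symptom under a strict new-only form. If the form grades every item at both times, nothing is lost at data collection, and only the stated use of the data is too narrow.

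**The case against.** **No scoring rule is printed.** A reader might infer that a worsening participant is scored as having no adverse effect. The article does not say so. It describes a screen by the investigators, not a count of events. What can be said is that such worsening lies outside what is asked and screened. This objection stands and limits the claim.

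**The data may be there after all.** A reader might also infer that worsening can never be recovered. The documents do not establish that. A listed-symptom form completed before enrollment and again at discharge, on a scale whose lowest level is no bother at all, makes best sense if every item is graded both times. This stands too: the loss is conditional on the form following the text.

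**The article is a condensation.** The form and the adverse-event definitions may sit in the full protocol, and their absence here is no finding. But the point does not rest on an absence. The article states what is asked, what is graded and what the result is used for, and all three are limited to new symptoms.

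**The safety comparison need not be biased.** A reader might infer a bias toward no difference between arms. Suppose new or worse symptoms truly occur in 10 % on placebo and 25 % on melatonin whatever the baseline status, and only new ones are recorded. Each rate is then multiplied by 1 − *b*. At *b* = 10 %, 30 % and 50 % the recorded rates are 9 % versus 22.5 %, 7 % versus 17.5 %, and 5 % versus 12.5 %. The difference shrinks from 15 points to 13.5, 10.5 and 7.5, but the risk ratio remains 2.5 throughout. Every input is assumed, and the article states no between-arm test of adverse effects, so a loss of power cannot be charged to the plan.

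**Safety does not rest on the checklist alone.** The HADS, the recording of psychotropic use and an independent monitoring committee all contribute. This is fair for anxiety and partly so for sleep. It does not reach headache, tremor or gastrointestinal symptoms.

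**Conclusion.** The point holds as a limited one about how adverse effects are ascertained. As written, the checklist asks about, grades and screens new symptoms only, although its timing and scale would allow change from baseline to be seen. If the discharge form follows the text, worsening of pre-existing insomnia, headache or gastrointestinal symptoms is outside the screen and its grade may not be recorded.

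The size is unknown. The illustration runs from about 1 to about 16 missed participants per group for one symptom, and that range reflects the assumed prevalence and worsening rates, not anything in the documents. The primary outcome, sample size and alpha are not touched.

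**What to change.** In the section on data monitoring and safety, state that every listed symptom is graded on the existing four-level bother scale at both completions, whether or not it is new. State also that symptoms that are new, or at least one grade worse than the participant's pre-enrollment grade, are screened for attribution and reported by arm. Make the discharge form match.

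The cost is one sentence and a small edit to the form, with no extra visit, instrument or staff. The trial status section says recruitment had not begun, so the change could apply to every participant. The downside is that worsening caused by the surgery itself will be counted. It will be counted in both arms, and the comparison with placebo handles it.

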#### Establishing the presence of delirium

The CAM will be used to establish the presence of delirium. The first assessment will take place in the pre-assessment clinic or hospital ward prior to the surgery (usually a week before but this can vary) and then daily, beginning 1 day post surgery and continuing for up to 7 days or until discharged (whichever comes first). The CAM was developed in 1988–1990 and is a widely used and well-validated screening tool for delirium, with sensitivity of 94 % (95 % CI 91–97 %) and specificity of 89 % (95 % CI 85–94 %) [37]. A trained research nurse will rate the scale on the basis of a standardized interview with the patient that includes a brief cognitive assessment. Case notes and nursing staff reports will be reviewed as part of the assessment. The diagnosis of delirium will be confirmed in consultation with an experienced psychogeriatrician ([name] or [name]). The CAM rates nine areas (acuity, attention, thought organization, level of consciousness, orientation, memory, perception, psychomotor tempo and sleep), but delirium is only diagnosed when there is evidence of acute onset, inattention, fluctuating mental state and either disorganized thinking or disturbed consciousness. The CAM has been successfully adapted for use in the intensive care setting [38]. The rating of the CAM takes about 10 minutes to complete.

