
### Participant timeline and recruitment

Table 1 shows the trial assessment schedule and Fig. 2 summarizes the recruitment and the flow of participants in the trial. Participants will be approached in pre-assessment clinics (all patients attend these a week or so prior to the scheduled surgery) and general hospital wards for those already hospitalized and awaiting surgery (i.e., semi-elective cases). Enrolled participants will be seen daily following their surgery with the primary outcome of interest being the difference in the incidence of delirium between the two groups. The final hospital assessment will occur on day 7 following surgery or the day of discharge (whichever comes first). Participants will be followed up one more time at 3 months after surgery to assess for the presence of delirium and to measure cognitive function.

**Table 1 Tab1:** Summary of trial assessment schedule

	Baseline	Daily	Discharge/7 days post surgery	3 months
Demographics	x			
Medical comorbidities	x			
Medications	x		x	
Surgery details			x	
Referral to mental health and geriatric services			x	
AUDIT	x			
LOS			x	
Adverse events	x		x	
CAM	x	x	x	x
MDAS	x	x (if required)	x (if required)	x (if required)
TICS-m	x		x	x
HADS	x		x	x

*AUDIT* Alcohol Use Disorders Identification Test, *CAM* Confusion Assessment Method, *HADS* Hospital Anxiety Depression Scale, *LOS* length of stay, *MDAS* Memorial Delirium Assessment Scale, *TICS-m* Telephone Interview for Cognitive Status-modified

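### Adverse effects are asked about only once after dosing starts, by participant recall over up to about two weeks, although a nurse already interviews each participant daily after surgery

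*Protocol article*

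**What the plan says.** The Data monitoring and safety section describes a symptom checklist answered by the participant: "The participants will be asked about the emergence of any new symptoms since the last assessment and how much they have been bothered by them". Its timing is fixed: "The checklist will be completed prior to enrollment and at discharge". Its purpose is also stated: "The investigators will use this to screen for any new symptoms that could be attributed to the study medication".

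Table 1 (Participant timeline and recruitment) agrees that there are two occasions. Adverse events are marked under Baseline and under "Discharge/7 days post surgery". The Daily and 3-month cells are empty.

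The same article already provides daily contact: "Enrolled participants will be seen daily following their surgery". Under Establishing the presence of delirium, the delirium assessment is made "daily, beginning 1 day post surgery and continuing for up to 7 days or until discharged (whichever comes first"), and "A trained research nurse will rate the scale on the basis of a standardized interview with the patient". Case notes and nursing reports are reviewed for that assessment. The article does not say that they are reviewed for adverse effects.

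**The concern.** The safety checklist depends on one retrospective self-report, in a trial whose primary outcome is a disorder of attention and cognition. Three things are at stake.

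- **Dating.** One interview spans the pre-operative doses, the operation, intensive care and the ward. The article describes no onset date, and any date asked for at that point would come from memory. It is then hard to separate symptoms that began before, during or after dosing, which weakens a screen meant to find symptoms attributable to the drug.
- **Informant.** A participant who has been delirious may recall the period poorly. If melatonin changes the frequency of delirium, the quality of recall could differ between arms.
- **Missing forms.** A participant who dies before the second checklist contributes no symptom data after the first dose.

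The daily nurse interview could supply this information and is not used for it.

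**Working it through.** No stated figure is in dispute, so the check sets the sections side by side and works out the look-back period.

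**Inputs**
- Dosing (Interventions): seven nightly doses, the first two nights before surgery. With surgery as day 0, these are nights −2, −1, 0, +1, +2, +3 and +4.
- Baseline (Establishing the presence of delirium): usually about a week before surgery, but variable. I take day −7 for the calculation and assume that the pre-enrolment checklist is completed then.
- Final in-hospital assessment (Participant timeline and recruitment): day 7 or discharge, whichever comes first.
- Daily visits: day 1 to day 7 or discharge.
- Planning rates (Sample size): delirium in 25 % of controls and 9.4 % on melatonin, 105 recruited per arm.

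**Look-back as planned.** I read the last assessment as the last time the checklist was completed, which is baseline.
- Total: 7 days before surgery + up to 7 after = up to 14 days.
- Before any drug: day −7 to night −2 = 5 days.
- After the first dose: night −2 to day 7 = 9 days.
- With discharge on day 5, for example, these become 7 + 5 = 12 days in total and 2 + 5 = 7 days after the first dose. If baseline is b days before surgery, the total is up to b + 7. Postponed surgery, which the article anticipates, lengthens it.

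**Look-back with daily completion**
- The day 1 form still covers 7 + 1 = 8 days and the doses of nights −2, −1 and 0.
- Each later form covers 1 day. The doses of nights +1 to +4 are each followed by a form the next day, while the participant remains in hospital.

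**How many might report after a delirium.** On the planning rates:
- control: 105 × 0.25 = 26.25, about 26;
- melatonin: 105 × 0.094 = 9.87, about 10.

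These are expected numbers with any delirium within 7 days. They are not counts of participants whose recall has failed.

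**Deaths.** Under Measuring morbidity and lifestyle, participants who die after surgery form their own discharge group, so some deaths are foreseen, but no rate is given. If 1 % to 5 % died before the final in-hospital assessment (an assumption), 210 × 0.01 = 2.1 to 210 × 0.05 = 10.5, or about 2 to 11 participants, would have no post-dose checklist.

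**The case against.** The strongest reply is that light symptom monitoring is a defensible choice. The article cites a safety profile comparable to placebo and earlier trials supporting the tolerability of the 3 mg dose, and only seven doses are scheduled. The checklist is described as a screen; no comparison of symptoms between arms is listed among the outcomes or analyses. That stands, and it limits the weight of the point.

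A reader might infer more than the documents support:

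- **That deaths or serious adverse events go unrecorded.** Deaths are recorded as a separate group, and serious-event reporting may be set out in the full protocol. Only the symptom checklist of those who die before the final in-hospital assessment is lost.
- **That recall is unreliable in 25 % of one arm and 9 % of the other.** Those are assumed delirium rates. Delirium fluctuates, and the article does not say how many would still be impaired, or unable to recall, at the final visit. Which arm would report more is conjecture.
- **That the checklist's timing is contradictory.** The safety section says discharge where Table 1 also allows day 7, but the timeline section settles the final hospital assessment as whichever comes first. The wording is loose and worth aligning. On that reading a long-stay participant is asked about three days after the night +4 dose.
- **That daily asking cuts recall to one day throughout.** It does so only from day 2; the day 1 form still looks back about 8 days.
- **That the monitoring committee's data would be late.** It meets twice a year, and nothing says that the checklist is its only input.

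It is also fair to object that a delirious participant cannot report well on the day either, and that using the chart only for those who cannot answer would make ascertainment depend on delirium. The fix has to meet this by reviewing the chart for everyone.

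**Conclusion.** The point holds as a design improvement. Adverse effects are gathered by one participant-recalled checklist after dosing starts. It covers up to about 14 days, about 9 of them after the first dose, assuming baseline about 7 days before surgery and a final assessment on day 7. Symptoms during dosing therefore cannot be reliably dated, and recall may be poorer after delirium, with any bias between arms unknown in size and direction. Deaths before the final in-hospital assessment leave no post-dose checklist; their number rests on an assumed mortality. The article itself fixes this schedule, so it is not a detail left to another document. Recruitment had not begun, so a change could apply to every participant.

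**What to change.** - In Table 1, mark adverse events in the Daily column.
- In Data monitoring and safety, have the nurse complete the checklist at each existing post-operative visit, day 1 to day 7 or discharge, with an onset date for each new symptom.
- Review case notes and nursing reports for the checklist in all participants, not only those who cannot answer, so that ascertainment does not depend on delirium.
- Have the day 1 form ask separately about the pre-operative doses.
- State that the final checklist is at day 7 or discharge, whichever comes first, to match the timeline section.
- For participants who die or withdraw, use the daily checklists completed so far.

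The cost is a few minutes at a visit already planned and a longer form, with no new visit or staff. More minor post-operative symptoms will be recorded. The pre-operative doses remain covered by a look-back of about 8 days.
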